## Abstract

**Background:**

In India, hanging is the leading method of suicide, and survivors of near-hanging often present with altered sensorium due to cerebral edema from cervical vascular compression and hypoxia. Management typically involves supportive care and antiedema measures, such as mannitol, hypertonic saline, and dexamethasone. Dexamethasone, a corticosteroid that crosses the blood-brain barrier, is commonly used for presumed cerebral edema. However, evidence supporting its efficacy is limited, and there are no clinical guidelines that recommend its routine use. A randomized controlled trial is therefore essential to establish the real-world efficacy of dexamethasone in this setting.

**Objective:**

The primary objective of this study is to evaluate the efficacy of intravenous dexamethasone, compared with placebo, in achieving good neurological outcomes at day 28. Secondary objectives are to assess the efficacy of dexamethasone, compared with placebo, in improving neurological outcomes at hospital discharge. We will also compare the duration of hospital stay and the incidence of in-hospital complications between patients receiving dexamethasone and those receiving a placebo.

**Methods:**

The CHANGING trial (Corticosteroids in HANGING) is a multicenter, double-blind, randomized, placebo-controlled study at 3 Indian tertiary centers. It enrolls 192 near-hanging patients with a Glasgow Coma Scale score ≤13 over 3 years, randomizing them in a 1:1 ratio to IV dexamethasone or placebo, plus standard care for 3 to 5 days. The primary outcome is neurological recovery at day 28, assessed using the Glasgow Outcome Scale. Secondary outcomes include the Glasgow Outcome Scale at discharge, duration of hospital stay, and the incidence of in-hospital complications. This trial has been approved by Jawaharlal Institute of Postgraduate Medical Education and Research, Puducherry Institute Ethics Committee (January 22, 2025), with subsequent approvals from Indira Gandhi Medical College and Research Institute (April 8, 2025) and Postgraduate Institute of Medical Education and Research (August 26, 2025).

**Results:**

The study commenced in October 2025 and is planned to be completed by May 2028. It is currently ongoing, and patient recruitment is in progress. Results will be analyzed after completion of enrollment and follow-up and will be disseminated through peer-reviewed publications.

**Conclusions:**

Corticosteroids are widely used for cerebral edema after near-hanging, but their role is unclear. The CHANGING trial will test dexamethasone’s efficacy and safety in these patients to guide future practice and guidelines.

## Introduction

### Background

Suicide is a major global health issue, with over 700,000 deaths in 2019 [1]. In India, hanging accounts for 58.2% of suicides, making it the leading cause [2]. Fatal hanging causes immediate death, while nonfatal (or near-hanging) cases survive the attempt and manage to reach the hospital [3]. Patients surviving near-hanging often have varying degrees of injury to vital neck structures, often requiring intensive care. Key management focuses on airway protection, aspiration pneumonia, pulmonary complications, and cervical spine injury; preventing secondary brain injury caused by reperfusion after the release of the obstruction; and treating cerebral edema and hypoxic damage [4-8]. Neurological injury in the form of cerebral edema critically affects long-term outcomes [4,7,8].

Brain injury caused by near-hanging is due to cerebral hypoxia resulting from airway obstruction, compression of the carotid arteries, compression of the jugular veins, or a combination of these mechanisms. Secondary brain injury due to reperfusion further worsens brain damage [5,9]. The damage occurs through several processes, including inflammation, oxidative stress, damage to brain cells, and disruption of the blood-brain barrier, causing cerebral edema. Cerebral edema can further increase once compression is relieved and blood flow returns [10-12]. This cerebral edema may represent a therapeutic target, as it is a potentially reversible component of brain injury. This edema can be due to cytotoxic edema (cellular energy failure leading to intracellular water accumulation) or vasogenic edema (leakage of fluid into brain tissue after damage to the blood-brain barrier), and both types may occur together [10-13]. Although direct evidence in near-hanging is limited, these processes are well described in hypoxic brain injury, traumatic brain injury, ischemic stroke, high-altitude cerebral edema (HACE), and other neurocritical illnesses [14-17].

Corticosteroids, such as dexamethasone, are favored for their blood-brain barrier penetration and reduce vasogenic cerebral edema by stabilizing the blood-brain barrier, reducing endothelial permeability, and suppressing inflammation [14,18]. They are effective in conditions such as brain tumors and bacterial meningitis, but their role in acute brain injury remains doubtful. The Medical Research Council CRASH (Corticosteroid Randomization after Significant Head Injury) trial demonstrated increased mortality in traumatic brain injury with the use of corticosteroids [19].

Corticosteroids are used to treat cerebral edema in near-hanging patients with altered sensorium, despite limited evidence [20]. Their proven role in HACE, involving hypoxia- and inflammation-driven edema, prompts extrapolation to hanging cases [15-17]. As the pathophysiology of hanging-induced cerebral edema is poorly understood, this analogy is theoretical.

A retrospective study from a South Indian tertiary care center admitted 323 near-hanging patients over 5 years, most of whom were young-or middle-aged men. Steroids were given to 68% (219/323) of patients, mainly dexamethasone (200/219) [17]. Among patients with Glasgow Coma Scale (GCS) ≤13 cases (n=201), steroid recipients (n=160, 80%) had 77% good outcomes vs 90% in nonrecipients (n=41, 20%), but selection bias favored administering steroids to sicker patients, and steroid dosing and duration varied. No established guidelines exist for managing near-hanging, including steroid use, which contributes to wide practice variations [21].

### Study Rationale

At present, the use of corticosteroids in near-hanging patients with impaired consciousness is inconsistent and guided largely by individual clinicians’ preferences and assumptions about shared pathogenesis with other traumatic brain injuries and similar conditions, rather than by evidence-based recommendations. There are no established guidelines or randomized controlled trials addressing this therapeutic dilemma. This lack of clarity creates genuine clinical equipoise regarding the role of steroids in managing cerebral edema following near-hanging, underscoring the urgent need for high-quality prospective evidence.

### Expected Outcome

This study aims to systematically evaluate the efficacy of steroid therapy in near-hanging patients with altered sensorium. The findings are expected to generate evidence that may guide clinical decision-making and contribute to the development of standardized treatment recommendations.

### Objectives

The primary objective of this study is to evaluate the efficacy of intravenous dexamethasone, compared with placebo, in achieving a good neurological outcome (Glasgow Outcome Scale [GOS] 4‐5) at day 28 in patients presenting with near-hanging with altered sensorium. Secondary objectives are to assess neurological outcomes at hospital discharge, compare the length of hospital stay, and compare the incidence of in-hospital complications between the dexamethasone and placebo groups.

## Methods

### Overview

The CHANGING trial (Corticosteroids in HANGING) is a multicenter, double-blind, randomized, placebo-controlled clinical trial designed to evaluate whether intravenous dexamethasone improves neurological outcomes in patients presenting with near-hanging. This protocol has been designed in accordance with the SPIRIT (Standard Protocol Items: Recommendations for Interventional Trials) 2013 statement (Checklist 1) to ensure robust and transparent reporting of the study methodology [22,23]. The flow chart depicting the various stages of the study is shown in Figure 1.

### Study Organization

The primary site, Jawaharlal Institute of Postgraduate Medical Education and Research (JIPMER), Puducherry, is the coordinating site. The principal investigator and coinvestigators at the primary site were involved in protocol development and securing funding for this trial from the Indian Council of Medical Research (ICMR), New Delhi. The primary site will conduct training, data monitoring, randomization, and quality control for the other 2 sites, Indira Gandhi Medical College and Research Institute (IGMCRI), Puducherry, and Postgraduate Institute of Medical Education and Research (PGIMER), Chandigarh. All 3 sites will competitively recruit consecutive patients admitted with near-hanging. All sites are responsible for following the protocol and ensuring the quality of the data collected.

**Figure 1. F1:**
[figure not shown]
Flow chart depicting the various stages of the study.

### Study Setting

This trial will be conducted in the Departments of Medicine and Emergency Medicine at 3 tertiary care centers in India: JIPMER, Puducherry; IGMCRI, Puducherry; and PGIMER, Chandigarh.

### Study Participants

Patients with near-hanging presenting to the emergency medicine departments of 3 study centers—JIPMER, Puducherry (JI); IGMCRI, Puducherry (IG); and PGIMER, Chandigarh (PG)—will be the study participants.

### Eligibility Criteria

The inclusion and exclusion criteria for the study participants are shown in Textbox 1.

Textbox 1.Inclusion and exclusion criteria for study participants.
**Inclusion criteria**
Age ≥18 years.History of near-hanging.Altered sensorium with Glasgow Coma Scale (GCS) ≤13 at presentation.Presentation to the hospital within 48 hours of the hanging event.
**Exclusion criteria**
Concurrent use of other methods of suicide.Active tuberculosis, HIV infection, recent systemic steroid use, other immunosuppressive therapy, or any definite indication or contraindication to corticosteroid therapy.Known hypersensitivity to dexamethasone or study-related drugs.Pregnancy or breastfeeding.Pre-existing neurological disorders.Hanging-related cervical spine injury.Moribund state where survival is deemed unlikely irrespective of intervention.

### Randomization and Allocation Concealment

Central randomization will be conducted at the coordinating center. Participants will be randomly allocated in a 1:1 ratio to receive either intravenous dexamethasone or placebo using a computer-generated randomization sequence. Variable block sizes of 4 and 6 will be used, with stratification based on baseline GCS score (≤8 and >8) to ensure balance between the treatment groups. Allocation concealment will be ensured using the Sequentially Numbered Opaque Sealed Envelopes method.

The study medications (dexamethasone or placebo) are prepared in identical-looking vials and labeled with a 5-character alphanumeric code using a randomly generated sequence, as shown in Figure 2. They are securely packed in designated boxes for each site. The random sequence used for labeling the study medications is stored in a password-protected Microsoft Excel sheet, accessible only to an unblinded investigator at the primary site to ensure confidentiality and maintain blinding throughout the study.

**Figure 2. F2:**
[figure not shown]
Medication kit. The left panel shows that a box is labeled with a randomly generated 5-character alphanumeric sequence. The right panel displays the sample medication kit with the same label.

A designated coinvestigator who is the only unblinded person other than the study statistician at the primary site will assume responsibility for crucial aspects of randomization, allocation concealment, and maintenance of the blinding process. All other staff (investigators, nurses, outcome assessors, and research team) and participants remain blinded to treatment assignments throughout the trial. After eligibility confirmation and written consent, the site team contacts the unblinded coinvestigator at the coordinating center. This investigator reconfirms eligibility and consent, performs randomization, and shares only the study drug label number supplied to each site, never revealing the actual treatment allocation.

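### Concealment is not assured at the central step, because the unblinded coinvestigator reconfirms eligibility just before randomizing

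*Protocol article*

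**What the plan says.** All of this stands in the Protocol article, mainly under Methods, Randomization and Allocation Concealment (including the text after the Figure 2 caption).

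- **Method.** Randomization is central, 1:1, in blocks of 4 and 6, stratified by baseline GCS (≤8, >8). Site is not a stratum. "Allocation concealment will be ensured using the Sequentially Numbered Opaque Sealed Envelopes method".
- **Kit code.** Vials carry a random five-character label and are boxed by site. The sequence used for labeling is in a password-protected sheet "accessible only to an unblinded investigator at the primary site".
- **The unblinded role.** It falls to one person: "A designated coinvestigator who is the only unblinded person other than the study statistician at the primary site". The same person is put in charge of randomizing, of concealment and of keeping the blind.
- **Order of events.** "After eligibility confirmation and written consent, the site team contacts the unblinded coinvestigator at the coordinating center". Then: "This investigator reconfirms eligibility and consent, performs randomization, and shares only the study drug label number supplied to each site". The treatment itself is never disclosed to the site.
- **Criteria being rechecked.** Textbox 1 includes "Moribund state where survival is deemed unlikely irrespective of intervention", as well as any definite indication for, or contraindication to, corticosteroids.

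**The concern.** Allocation is concealed when whoever can still keep a patient out of the trial neither knows nor can predict the next assignment. Site staff meet that condition. The unblinded coinvestigator may not: this person checks eligibility again, immediately before allocation, while able to know what earlier patients received. Two of the exclusions call for judgement, and the moribund criterion is strongly tied to the primary outcome. A doubtful case could be read one way or the other, without any intent, according to the arm expected next.

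Selection before randomization cannot be repaired later. Blinded outcome assessment does not touch it, and an intention-to-treat analysis includes only those who were randomized. The Discussion relies on random allocation and blinding to minimize selection bias, so the weak step bears on a strength the trial claims.

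**Working it through.** The protocol gives no figure for predictability, so there is none to reproduce. The check has two parts.

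**1. Who knows what at the reconfirmation step**

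- The label-to-treatment key is open only to an unblinded investigator at the primary site. The designated coinvestigator is the only unblinded person there besides the study statistician. The natural inference is that they are the same person.
- Kits are boxed by site, but the sequence is stratified only by GCS. Each assignment must therefore be matched to a kit held at the calling site, which plausibly requires the code-holder to know the arm each time.
- So this person can know all earlier assignments. Whether the next one is also visible is not stated. The sheet is described as a labeling key, not as the list of assignments in patient order, and the article does not say who prepares, holds or opens the envelopes.

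**2. How predictable the next assignment is if the envelope is still sealed**

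Inputs from the protocol: 1:1 allocation, block sizes 4 and 6, two strata. Assumptions: the two block sizes are equally frequent; the guesser picks the arm that is more likely given past assignments and tosses a coin when the two are equally likely.

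*Correct guesses, block ends known.* In a block of 2m the expected number correct is m − 1/2 + 2^(2m−1)/C(2m, m).

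- Block of 4 (m = 2): 2 − 0.5 + 8/6 = 2.833 of 4, or 70.8%
- Block of 6 (m = 3): 3 − 0.5 + 32/20 = 4.1 of 6, or 68.3%
- Equal mix: (2.833 + 4.1)/(4 + 6) = 6.933/10 = **69.3%**, against 50% by chance

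*Assignments fixed by the rest of the block, block ends known.* The expected number is 2m/(m + 1).

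- Block of 4: 4/3 = 1.333, or 33.3%
- Block of 6: 6/4 = 1.5, or 25.0%
- Equal mix: (1.333 + 1.5)/10 = **28.3%**

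*Block ends not known.* In a simulation of 1,000 trials with two strata of 96 (the split is assumed), the guesser knew only that blocks were 4 or 6 and updated exactly on past assignments.

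| What the guesser knows | Correct guesses | Certain assignments |
|---|---|---|
| Past assignments and block sizes (simulated) | 69.2% | 28.0% |
| Past assignments; only that blocks are 4 or 6 (simulated) | 69.1% | 5.5% |
| The patient-order list itself | 100% | 100% |

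The guess rate hardly depends on knowing the block ends; the share of certain assignments does. The last row follows by definition and applies only if this person can see the list, which the article does not say.

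**The case against.** A reader might infer that allocation is simply not concealed, or that the coinvestigator has the final say on who enters. The text does not support either.

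- Blinded site staff confirm eligibility and obtain consent first.
- The stated order is reconfirm, then randomize, which fits a check completed before the assignment is revealed. Sealed envelopes are named, and may be opened only at that point.
- To reconfirm may mean no more than checking that the form is complete. The article grants no power to overrule the site.
- Screening logs and recorded exclusion reasons (Data Collection and Management; Screening, Informed Consent, and Enrollment) mean that a consented patient turned away centrally would be known to the site.
- Central randomization and envelopes are compatible, since the center can hold the envelopes. Who handles them is detail that an article may leave to the full protocol.

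Most of this stands, and it limits the point to one step. It does not remove it. A sealed envelope hides the next assignment but not the past ones, and past assignments in small blocks are enough for the 69%. A reconfirmation that could never change the outcome would have no purpose, so some discretion must be presumed. The logs make a refusal visible, but the article does not separate refusals at the site from those after contact with the unblinded person. At submission 16 patients had been screened and 3 enrolled, so one further exclusion would not stand out.

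**Conclusion.** The point holds in a limited form: concealment is not assured at the central reconfirmation step. An unblinded person who can know earlier assignments rechecks criteria that need judgement, and can guess the next assignment about 69% of the time. Between about 5.5% and 28% of assignments are certain, depending on whether block ends are known.

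This rests on three readings: that the key-holder and the coinvestigator are the same person, that this person keeps track of past assignments, and that the block sizes are mixed about equally. The last matters little, since with block ends known any mix gives between 68.3% and 70.8%.

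The percentages measure opportunity, not bias. The documents offer no basis for saying how many patients would be affected or how far the day-28 result would move, and nothing in them suggests misconduct. This is a cheap improvement, best made now: at submission 3 of 192 patients had been enrolled and two sites had not started.

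**What to change.** Amend the description of the randomization call under Randomization and Allocation Concealment:

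1. Blinded site or coordinating-center staff confirm eligibility, consent and GCS stratum and lock them with a time stamp in the existing REDCap database before the unblinded coinvestigator is contacted.
2. The unblinded coinvestigator has no eligibility role. This person opens the next envelope for the stratum and issues the label of a matching kit held at that site.
3. Any patient not randomized after contact is logged with the reason.
4. One clause states how the envelopes fit with central release of the label: who holds them, and that each is opened only after the lock.

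There is no need to delete either mechanism or to move a running trial to a new randomization system. The cost is one added database field and a procedure amendment through the three ethics committees. Sample size stays at 192.

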### Trial Treatment

#### Study Interventions

All patients will receive standard medical care for near-hanging. Standard medical care includes head-end elevation, anticerebral edema measures using either mannitol or hypertonic saline, mechanical ventilator support (if required), and vasopressor support (if required)

Participants will be treated with the IV study drug for a minimum period of 3 days and a maximum of 5 days. The study drug can be stopped after a minimum of 3 days of therapy if the patient’s sensorium has improved to a GCS score of 15. Tapering of steroids (or placebo) is not required, as the duration of therapy is short. If steroids are stopped but cerebral edema causes a worsening of sensorium, steroids can be restarted, and this will be recorded.

#### Trial Treatment Schedule

This clinical trial compares 3 to 5 days of treatment with IV dexamethasone 8 mg stat, followed by 4 mg every 6 hours daily vs placebo, as shown in Textbox 2. This dose is adapted from the HACE treatment protocol, in which hypoxia similarly leads to cerebral edema [15].

Textbox 2.Trial treatment schedule
**Day 1**
Dexamethasone arm: dexamethasone 8 mg IV administered as a slow IV push stat followed by 4 mg every 6 hours.Placebo arm: identically looking placebo of similar volume administered slow IV push similar to the dose of dexamethasone.
**Day 2 and 3**
Dexamethasone arm: dexamethasone 4 mg every 6 hours.Placebo arm: placebo IV every 6 hours.
**Day 4**
Assessment on day 4 to determine whether dexamethasone or placebo should be continued (based on GCS).
**Day 4-5 assessment**
Dexamethasone arm: dexamethasone 4 mg IV every 6 hours.Placebo arm: placebo IV every 6 hours.

#### Premature Discontinuation of Randomized Treatment

The planned duration of study drug administration is 3 to 5 days. Earlier neurological recovery (GCS 15/15) is expected in some participants; a predefined, protocol-specified tapering or discontinuation strategy will be followed to minimize unnecessary drug exposure, as shown in Table 1.

**Table 1. T1:** Premature discontinuation of randomized treatment.

Day when GCS^a^ 15/15 is first attained	Assessment time point	Study drug to be continued until
Day 1	6th, 12th, or 18th hour	Corresponding time points on day 2: 6th, 12th, or 18th hour (additional 24 hours)
Day 2	Any time point	Day 3
Day 3 or 4	Any time point	Based on clinical assessment by the study team
Day 5	–^b^	No further study drug will be administered

a GCS: Glasgow Coma Scale.

b Not applicable.

#### Mandatory Discontinuation

Study treatment will be permanently discontinued at any time if a participant develops a definite indication for or contraindication to dexamethasone or if discontinuation is clinically indicated, as determined by the treating investigator.

Premature discontinuation of study treatment will not affect protocol-mandated follow-up. All randomized participants will continue follow-up as per the approved study schedule.

### Investigational Product Management

#### Overview

The investigational products, dexamethasone and placebo, have been procured from a Good Manufacturing Practice (GMP)-certified pharmaceutical manufacturer, Jackson Laboratory Pharmaceutical Company, with dexamethasone supplied as a 4 mg/2 mL injectable solution in plain glass vials. The placebo consists of an equivalent volume (2 mL) of normal saline for injection, supplied in identical glass vials to ensure blinding.

A kit of study medication, comprising 22 vials for each patient, is assigned a unique 5-character alphanumeric identifier. The medication kit with the labeled vials is shown in Figure 2.

Manufacturing details, expiry dates, and recommended storage conditions have been communicated to investigators at all participating sites, and relevant documentation has been shared for regulatory and monitoring purposes.

Drug distribution is centrally coordinated by a designated coinvestigator at the coordinating center. The first batch of study medication has been supplied to all participating centers with sufficient buffer stock to support recruitment for the initial 2 years. Additional batches will be procured and distributed as needed, aligned with expiry timelines. Each site will maintain a drug accountability log documenting receipt, dispensing, and disposal. Unused or expired study medication will be discarded according to institutional biomedical waste management protocols.

